The primary aim of this on-going randomized trial is to assess the efficacy of a culturally and linguistically tailored telephone-delivered intervention to increase adherence to physician-recommended assessment and treatment of sleep apnea. The secondary aims are to: 1) evaluate the maintenance of intervention effects on adherence at 6 months post-randomization; and 2) assess treatment effects on indices of the metabolic syndrome (waist circumference, blood pressure (BP), lipid levels and fasting plasma glucose (FPG) or hemoglobin (HbA1c) for those who have a DM diagnosis). There are four main hypotheses for this study: 1) participants will show greater adherence to physician-recommended polysomnographic sleep apnea evaluation during follow-up assessment; 2) participants will show greater adherence to CPAP treatment during follow-up assessment; 3) effects of the intervention on adherence rates will be maintained 6 months after discontinuing active interventions, and treatments will improve indexes of the metabolic syndrome; and 4) participants’ knowledge about sleep, self-efficacy, readiness, and trust/rapport with the health educator (HE) will mediate intervention effects on study outcomes. The study is registered in clinicaltrials.gov.

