#### Adherence to CPAP

We will assess CPAP adherence using subjective and objective measures. A self-report scale will be used to track CPAP adherence at the end of the 6-month period. CPAP adherence is defined as the mean number of hours per day and days per week participants report using CPAP [35,36] (adherence: > 4 hours a night for 70% of the nights or no report of symptomatic complaints). Throughout the study, CPAP adherence data will be electronically monitored on a daily basis. Data will be downloaded directly from CPAP devices [37].

A complete list of measures and the data collection schedule is provided in Table 2.

**Table 2 T2:** Schedule to acquire study data

**Outcome measures**	**Baseline**	**First follow-up**^ **a** ^	**Second follow-up**
Sociodemographic and clinical variables	X		
Apnea-risk evaluation system questionnaire	X		
Epworth sleepiness scale		X	X
CES-D	X	X	
Apnea knowledge test	X	X	
Apnea beliefs scale	X	X	
Medical outcomes study short form 36	X		
Self-efficacy scale	X	X	
Change assessment scale	X		
Functional outcomes in sleep questionnaire	X	X	
Process variables	X	X	
*Post hoc* evaluation variables			X
Sleep variables (chart audit)		X	

^a^Follow-up outcome ascertainment is performed by the Data Manager at 6 months post-enrollment and at 6 months post-telephone intervention (TTI).

Cardio-metabolic measures are as follows. (1) Weight will be measured without shoes and using a validated digital scale. (2) Waist circumference will be measured by 1) locating the upper hip bone and the top of the right iliac crest, 2) placing the measuring tape horizontally around the abdomen at the level of the iliac crest (tape is snug without causing compression), and 3) measuring at the end of a normal expiration. (3) BP measurements will be taken following American Heart Association guidelines [38]. Using a BPTru automated BP monitor, five readings will be obtained while participants are seated comfortably for five minutes prior to measurement [39]; the average BP will be used as the BP index for each visit. (4) Following the National Cholesterol Education Program standard guidelines for total cholesterol measurement, we will use the Cholestech LDX Analyzer; whole blood from fingersticks will be used for the quantitative determination of HDL-C and FPG utilizing established formulation [40]. All measurements will be collected by trained clinical research staff.

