### Statistical analysis

To describe the characteristics of the study population, we will use measures of central tendencies and dispersion for continuous data; frequency distributions will be used for categorical data. Chi-square tests will be used to compare categorical data, and ANOVA will be used for continuous data. Relationships between mediators of adherence to recommended sleep apnea assessment and CPAP treatment will be examined using binary multivariate logistic regression analysis. The two main dependent measures will be: adherence to physician-recommended sleep assessment (yes versus no) and adherence to CPAP treatment (yes versus no). Candidate mediators will include sleep apnea knowledge, self-efficacy, readiness, and trust/rapport with the HE. Effects of sociodemographic and clinical factors will be adjusted in those analyses. Repeated-measures MANCOVA will be used to examine differences between baseline and follow-up measures (for example, waist circumference (WC), BP, HDL-C, FBG/HbA1c); age, sex, and sleepiness will be entered as covariates. MANCOVA is a robust technique that incorporates routines to account for heterogeneous variances, serial correlations, and variance inflation [41].

### Hypothesis 1

TTI will lead to higher rates of sleep apnea assessment at 6 months. A comprehensive assessment of sleep apnea will be defined by documentation of an appropriate medical and sleep history by a sleep clinician and a nocturnal polysomnographic study.

#### Analysis for hypothesis 1

Analysis will be performed on an intention-to-treat basis. All participants in the treatment arm will be assumed to have received the full dose of the telephone intervention and all participants in the attention-control arm will be assumed to have received no tailored intervention. Prior to testing for intervention effects, we will verify the comparability of the treatment and control arms with respect to all available demographic and personal data. T-tests and chi-square tests will be used for continuous and categorical variables, respectively. Thus, receipt of sleep apnea assessments within the 6-month period will be a binary outcome, yes or no. We will use logistic regression to estimate the odds associated with receipt of sleep apnea assessment contrasting the two study arms.

### Hypothesis 2

TTI will lead to higher adherence rates to recommended follow-up care (that is, CPAP use (> 4 hours a night for 70% of the nights)) post-diagnosis of sleep apnea.

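### No mediator score scheduled in both arms falls between randomisation and the sleep assessment, so mediation of the assessment outcome cannot be claimed from the planned regressions

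*Protocol article*

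**What the plan says.** The aims in the Background section state that "There are four main hypotheses for this study". The fourth is causal: knowledge, self-efficacy, readiness and "trust/rapport with the health educator (HE) will mediate intervention effects on study outcomes".

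The Statistical analysis section names the same four variables ("Candidate mediators will include sleep apnea knowledge, self-efficacy, readiness, and trust/rapport with the HE") and gives the method: "Relationships between mediators of adherence to recommended sleep apnea assessment and CPAP treatment will be examined using binary multivariate logistic regression analysis". The dependent measures are sleep assessment and CPAP adherence, each yes or no. Under Analysis for hypothesis 1, "receipt of sleep apnea assessments within the 6-month period will be a binary outcome". Power and sample size calculations claims 85% power for the mediators.

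On timing:

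- Table 2 marks the "Apnea knowledge test", the self-efficacy scale and the process variables at baseline and first follow-up. The table footnote and the Outcomes section put that follow-up at 6 months.
- Table 2 marks the readiness instrument (Change assessment scale) at baseline only. Trust/rapport has no named row.
- Under Randomization, allocation follows the baseline interview.
- Under Phase I, the health educator's calls begin within 2 weeks of randomisation.
- Under Follow-up procedures, the first sleep-centre visit includes a specialist consultation and an opportunity to ask questions. Diagnosed participants later receive information about the device.

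**The concern.** A mediator must be measured after the intervention has begun to act and before the outcome occurs. For assessment within 6 months, neither scheduled time meets both conditions. Baseline is too early, because randomised treatment cannot have changed the score. Month 6 is too late, because anyone who attended has already had the consultation, and some have had device teaching. Both could plausibly raise knowledge and self-efficacy.

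If attendance is regressed on 6-month scores, a positive coefficient may mean that attending raised the score and not that the score led to attendance. The trial could then credit its effect to the wrong component. The article intends to refine the intervention and disseminate it widely, so that error would have practical consequences.

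**Working it through.** **1. Can each named mediator be validly timed for assessment within 6 months?**

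| Mediator | Times in Table 2 | Problem |
|---|---|---|
| Knowledge | Baseline, 6 months | Before randomisation, or after any attendance |
| Self-efficacy | Baseline, 6 months | Same |
| Readiness | Baseline only | Cannot carry an intervention effect |
| Trust/rapport | No named row | If under process variables, same as knowledge |

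A change score from baseline to 6 months inherits the 6-month problem.

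**2. The plan's own figure.** The 85% mediator power cannot be reproduced, because no odds ratio per SD is stated. Inverting the single-covariate logistic formula with N = 340, mean rate P = (0.35 + 0.47)/2 = 0.41 and two-sided alpha 0.05:

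ln(OR) = (1.960 + 1.036) / √(340 × 0.41 × 0.59) = 2.996 / 9.07 = 0.330, so OR ≈ 1.39 per SD.

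This gives a yardstick for the artefact.

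**3. Size of the artefact.** Inputs from Power and sample size calculations are 170 per arm, 35% v 47% and two-sided alpha 0.05. One input is assumed: attending raises the score by d SD. The score has no effect on attendance, so true mediation is zero. Attendance is regressed on arm and the later score.

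Closed-form check: expected attenders are 170 × 0.35 + 170 × 0.47 = 139.4, and non-attenders 200.6. The standard error of the score difference is √(1/139.4 + 1/200.6) = 0.110. The chance of p < 0.05 is about Φ(d/0.110 − 1.96) + Φ(−d/0.110 − 1.96). The spurious OR per SD is about exp[d × √(1 + d² × 0.41 × 0.59)].

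| Assumed d (SD) | Closed form | Simulation | Spurious OR per SD |
|---|---|---|---|
| 0 | 5% | 4% | 1.00 |
| 0.1 | 15% | 13% | 1.11 |
| 0.2 | 44% | 41% | 1.22 |
| 0.3 | 78% | 78% | 1.35 |
| 0.5 | 99% | 99% | 1.67 |

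Repeat simulations differed by a few percentage points. Adjusting for the baseline score does not help. With an assumed baseline to 6-month correlation of 0.5, the false-positive share is 55% at 0.2 SD and 87% at 0.3 SD, with ORs of about 1.31 and 1.50. The second of these exceeds the 1.39 yardstick.

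If the intervention also raises the score by an assumed 0.3 SD without affecting attendance, adjusting for the score pulls the arm OR from about 1.65 to 1.52 (d = 0.2), 1.47 (d = 0.3) or 1.36 (d = 0.5). That fall would be read as mediation.

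**4. Is a lagged CPAP model sound?** Six-month scores do precede CPAP use in months 7 to 12, and "Throughout the study, CPAP adherence data will be electronically monitored on a daily basis". Early CPAP use could still raise the 6-month score and also persist. Simulations gave the score no effect on later use and assumed 80 to 139 CPAP users, a 0.3 to 0.5 SD rise from early use, and later-adherence rates differing by 0.5 to 0.7 between early adherers and non-adherers. Adjusting only for arm and baseline score gave false mediators in about 10% to 67% of trials. Adding adherence before month 6 brought this to about 4% to 6%.

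**The case against.** **The article does not say which scores enter the model.** This is true, and a condensed article may leave it to the analysis plan. A reader might infer that the plan commits itself to regressing attendance on later scores. The text does not say that. The point survives because each available choice fails: baseline scores cannot mediate, and 6-month or change scores follow the outcome. An analysis plan cannot create a score that was never scheduled.

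**Earlier measurements exist.** Under Phase I, the health educator assesses knowledge and readiness during calls, before attendance. It would therefore be wrong to say that every post-randomisation measurement comes too late. These assessments are described only for the tailored-intervention arm, and nothing links them to the regression. The Exit interviews section repeats the baseline questionnaires, but at the end of participation, so it does not help with timing.

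**The size is assumed.** This stands. All eligible participants receive brochures, and controls receive up to 10 informational calls, so attending may add little. At 0.1 SD the false-positive share is only about 13%.

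**The primary result is untouched.** This also stands. The comparison of assessment rates between arms does not use these scores.

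**Conclusion.** The point holds for mediation of the assessment outcome. A named main hypothesis cannot be validly tested on that outcome with the measurements scheduled in both arms. This conclusion rests on Table 2 and the 6-month outcome window and needs no assumed figure. The false-positive shares, from about 13% at 0.1 SD to about 99% at 0.5 SD, do rest on an assumed rise from attending.

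Three stronger readings are not supported:

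- That false mediation will be found. The document gives neither the model inputs nor the effect of attending on scores, so the regressions can mislead but need not.
- That all four mediators suffer reverse causation. It is shown for knowledge and self-efficacy, and is conditional for trust/rapport. Readiness has the opposite defect. The beliefs scale is on the same schedule but is not a named mediator.
- That mediation of CPAP adherence is ruled out as well. For months 7 to 12 the time order can be made sound, subject to the adjustment and selection limits set out above and in the fix.

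**What to change.** Change the wording of the analysis plan as follows.

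- For assessment within 6 months, use baseline scores only as predictors or moderators, report 6-month scores as associations, and make no mediation claim.
- For knowledge and self-efficacy, limit mediation claims to CPAP adherence in months 7 to 12 from device downloads. Adjust for arm, baseline score and CPAP adherence before month 6. State that the model covers diagnosed participants on CPAP, a subgroup selected after randomisation, and is exploratory.
- Do not call readiness a mediator while it is measured only at baseline.
- State where and when trust/rapport is measured. If it is a 6-month process variable, treat it as an association for assessment.

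No new visit is needed. The cost is that mediation of assessment is no longer claimed and the CPAP model uses fewer participants. Measuring mediators in both arms after the calls begin and before the sleep visit would address the timing directly. However, Trial status reports 311 already randomised, which leaves only 340 − 311 = 29 of the planned sample still to enter.

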### Theoretical framework

The intervention is guided by the transtheoretical model developed by Prochaska et al. (Figure 1) [21]. This behavior change model consists of five stages that the individual moves through in the process of modifying a problem behavior. The first stage begins with pre-contemplation, in which a person is not considering change and is often unaware that they have a problem to be modified; it continues to the maintenance stage, where the individual has successfully altered the behavior (for 6 months or more) and concentrates on maintaining this new way of life. Between these two stages, the person may contemplate change, prepare to change, and begin to act to initiate behavior change. This model has been applied to a variety of health behaviors, such as alcohol and substance use, smoking cessation, condom use, and weight loss [21]. Our study will examine the relationship between participants’ readiness to use CPAP at the beginning of the intervention with the success they are likely to achieve in increasing adherence to physician-recommended sleep apnea assessment and CPAP treatment.

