### Description of the attention-control arm

The standard of care for adults with sleep apnea includes a referral for a comprehensive assessment of sleep apnea and provision of standard print communications about sleep apnea produced by the National Institutes of Health and the AASM. Participants in the control arm will receive up to 10 phone calls from a RA to provide information about sleep apnea and information about available resources. During these phone calls, no tailored behavioral change strategies will be used. The periodic phone calls are consistent with current practice of many medical facilities that have adopted the policy of making multiple phone calls to remind participants of scheduled doctor’s appointments. In addition, instituting this procedure ensures that differences in adherence rates are attributed solely to the delivery of the intervention.

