#### Change assessment scale

This is a 32-item instrument that assesses a person’s readiness to change. Participants evaluate the extent to which they strongly agree or strongly disagree with various statements such as, 'I’ve been thinking that I might want to change something about myself' and 'I have problems and I really think I should work on them' [34].

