### Power and sample size calculations

Data obtained from a random sample of black participants recruited from the MetSO Cohort Study has provided a current estimate of the rate of comprehensive assessment of sleep apnea to be expected in the proposed study. Analysis of the data suggested that 47% of participants referred for sleep assessment would adhere to physician recommendations after exposure to TTI, whereas 35% of those in a control group agreed to undergo a sleep assessment. Thus, this represents the likely rate of adherence expected in our AC group. We propose to achieve an adherence rate of 47% among participants exposed to the TTI.

With an expected 12% increase in the adherence rate associated with the TTI, a standard error of 0.10%, and a sample size of 340, the study will be adequately powered (90%) to detect significant increase in the outcome measures using chi-square tests. The primary study outcome in this project is documented receipt of a sleep apnea assessment. A two-tailed test, with alpha = 0.05, comparing adherence rates of 35% with 47% requires 170 participants per group [42]. The precision estimated in that analysis is the approximate expected precision of study data. Specifically, a difference of 12% would be observed at chi-square = 21.03 with a 95.0% confidence interval of 3% to 20%. With the proposed sample size, the study will have 85% power to achieve a one-standard deviation increase in the odds ratio of adherence attributable to proposed mediators: sleep apnea knowledge, self-efficacy, readiness, and trust/rapport with the HE (expressed as continuous variables).

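### Two of the four mediators in Hypothesis 4, readiness and rapport with the health educator, are not supported by the planned measurements, and the 85% power sentence for mediators names no effect size

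*Protocol article*

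**What the plan says.** All references are to the protocol article.

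- **Mediation claim.** The fourth hypothesis in *Background* lists knowledge about sleep, self-efficacy and readiness, and ends: "trust/rapport with the health educator (HE) will mediate intervention effects on study outcomes". *Statistical analysis* repeats the list ("Candidate mediators will include sleep apnea knowledge, self-efficacy, readiness, and trust/rapport with the HE"). It says the relationships with the two binary outcomes, sleep assessment and CPAP adherence, "will be examined using binary multivariate logistic regression analysis", with adjustment for sociodemographic and clinical factors.
- **Readiness.** The instrument is the Change assessment scale: "This is a 32-item instrument that assesses a person’s readiness to change". In Table 2 the row "Change assessment scale" has one mark, under baseline. The apnea knowledge test and the self-efficacy scale are marked at baseline and at first follow-up. *Randomization* places assignment after the baseline interview. *Exit interviews* says that everyone fills in the baseline questionnaires again, without giving a date. *Theoretical framework* relates "readiness to use CPAP at the beginning of the intervention" to later success.
- **Rapport with the HE.** The HE delivers the tailored telephone intervention (TTI). In the attention-control (AC) arm, "Participants in the control arm will receive up to 10 phone calls from a RA". *Randomization* offers AC participants the TTI only after their 12-month assessment. No rapport instrument is described, and the process-variables row of Table 2 is not defined.
- **Power.** *Power and sample size calculations* claims "85% power to achieve a one-standard deviation increase in the odds ratio of adherence attributable to proposed mediators", with the mediators taken as continuous. No odds ratio is given.

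**The concern.** A mediator of a randomised effect must be something the intervention can change. It therefore has to be measured after randomisation, in both arms, and before the outcome it is meant to explain. On Table 2, readiness fails the first condition. Rapport with the HE fails the second, because it describes a relationship that only one arm is scheduled to have.

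Hypothesis 4 is one of four main hypotheses, so its result is likely to be reported as the mechanism of the intervention. A logistic model containing baseline readiness would estimate how well starting readiness predicts adherence. A model containing HE rapport would either lose the AC arm through missing values or, with a fixed value imputed for AC, mix rapport with arm. Neither is evidence of mediation.

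The power sentence adds to the difficulty. An odds ratio does not increase by a standard deviation in any sense that defines an effect size, so the 85% cannot be checked or used.

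**Working it through.** **1. Readiness: the sections side by side**

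| Source | Timing | Arms | Usable as a mediator? |
|---|---|---|---|
| Table 2 | Baseline, before randomisation | Both | No. The expected arm difference is zero by randomisation. |
| *Phase I* calls, HE rating of stage | During calls | TTI only | No. There is no AC counterpart. |
| *Exit interviews*, repeat of baseline questionnaires | Undated | Both | Only for outcomes that follow it. |

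Table 2 and *Exit interviews* disagree on whether the scale is repeated. If the exit interview comes after the 6-month outcome, the repeat cannot mediate that outcome.

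**2. Rapport with the HE**

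Scheduled HE contact exists in TTI only, and AC calls come from a research assistant. The baseline mark in the process-variables row cannot be a rating of an HE whom nobody has yet dealt with. A first-follow-up rating could exist in TTI, but AC would have no comparable referent.

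**3. The 85% power figure**

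The plan's figure cannot be reproduced, because it gives no odds ratio (OR) per SD. The closest sensible reading is an OR per one-SD increase in the mediator, so I solve for the OR that gives 85%.

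Inputs from *Power and sample size calculations*: N = 340; adherence 35% and 47%, average p = (0.35 + 0.47)/2 = 0.41; two-sided alpha 0.05. That alpha is stated for the primary comparison and is assumed here for the mediators. R² is the share of the mediator's variance explained by other covariates, and its values are assumptions.

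Formula: ln(OR per SD) = (z₀.₉₇₅ + z₀.₈₅) / √(N·p·(1−p)·(1−R²)), with z values 1.960 and 1.036.

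- Unadjusted: 2.996/√(340 × 0.41 × 0.59) = 2.996/9.069 = 0.330, so OR = **1.39**.
- R² = 0.1: 0.330/√0.9 = 0.348, OR = **1.42**.
- R² = 0.2: 0.330/√0.8 = 0.369, OR = **1.45**.
- HE rapport within TTI (n = 170, p = 0.47): 2.996/√(170 × 0.47 × 0.53) = 2.996/6.507 = 0.460, OR = **1.58**.
- CPAP adherence counts only diagnosed participants. If only those assessed can be diagnosed, there are at most 0.41 × 340 ≈ 139. Even at the most favourable adherence rate (assumed 50%), 2.996/√(139 × 0.25) = 0.508, OR = 1.66. The true figure would be larger still, since not everyone assessed is diagnosed.

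For the sleep-assessment outcome (N = 340, p = 0.41, unadjusted), power depends on the missing OR:

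| OR per SD | Power |
|---|---|
| 1.2 | 38% |
| 1.3 | 66% |
| 1.39 | 85% |
| 1.5 | 96% |

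**4. Association is not mediation**

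The 85% covers at most the path from mediator to outcome. The path from arm to mediator has power Φ(d·√(170/2) − 1.960), where d is an assumed arm difference in SD units. If both paths must be significant and are treated as independent, the joint power is that value times 0.85.

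| d | Arm-to-mediator power | Joint power |
|---|---|---|
| 0.2 | 45% | 39% |
| 0.3 | 79% | 67% |
| 0.4 | 96% | 81% |

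**The case against.** **Readiness.** A reader might infer that readiness is measured only before randomisation and so can never be tested as a mediator. The article does not support that. *Exit interviews* has all participants repeat the baseline questionnaires, which may give a post-randomisation value in both arms. Hypothesis 4 speaks of study outcomes generally, and these include 12-month maintenance, so a late measurement is not excluded for every outcome. Table 2 is also visibly incomplete: it has no rows for CPAP adherence, waist circumference or blood pressure. This stands. What remains is an unresolved conflict, and a repeat too late for the 6-month outcome if it follows it.

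**Theory.** *Theoretical framework* uses baseline readiness as a predictor, but *Description of the tailored telephone intervention* makes raising motivation the way the calls are meant to work. Readiness can moderate at baseline and mediate later. This also stands, so dropping it outright would be wrong.

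**Rapport.** It would go too far to say that AC participants never meet the HE. *Follow-up procedures* tells participants, without naming an arm, that the HE can answer questions. The full protocol may also define a rapport measure. Neither point supplies a comparable AC measure, because the control calls still come from someone else.

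**Power.** The 1.39 is solved back from 85% and is not a figure of the plan. Used alone, it would be wrong for adjusted models, for rapport within TTI and for CPAP adherence. That stands, so the figures must be given separately.

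**Mediation test.** The formal test may be left to the analysis plan. It may, but no test can make a baseline value or a one-arm relationship mediate.

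**Conclusion.** The concern holds in limited form. Two of the four named mediators are not supported as planned. Baseline readiness cannot mediate, and the article contradicts itself on whether readiness is measured again. HE rapport is fully tied to arm and cannot be tested as a two-arm mediator. Knowledge and self-efficacy have a first-follow-up measurement in Table 2 and are not part of this point.

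The power sentence is not a valid effect-size statement. The ORs in the working are what 85% power would correspond to, not values that the plan states. They describe association with adherence, and rest on the assumed alpha and R² values and on the planned adherence rates. The primary comparison of arms is unaffected.

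**What to change.** 1. Reconcile Table 2 with *Exit interviews*. State whether and when the Change assessment scale is repeated, and in which arms.
2. Use readiness as a mediator only for outcomes that follow a post-randomisation measurement in both arms. Otherwise analyse baseline readiness as an effect modifier (arm by baseline readiness), in line with *Theoretical framework*.
3. Analyse rapport with the HE within the TTI arm only, as a process predictor of adherence.
4. Replace the 85% sentence with detectable ORs per SD at 85% power, described as association with sleep-assessment adherence and not as mediation: about 1.39 unadjusted at N = 340 and 41% adherence (two-sided 0.05); about 1.42 to 1.45 if covariates explain an assumed 10% to 20% of the mediator; about 1.58 for HE rapport within TTI. Say that the value is larger than 1.39 for CPAP adherence, because only diagnosed participants count.

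The cost is almost entirely wording. With 311 participants already randomised, any added readiness measurement may reach only part of the sample, so re-labelling is the realistic route. The downside is that Hypothesis 4 claims fewer mediators and the power statement is less favourable.
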